#### Demographic data

Birth weight and gestation, race, ethnicity, and gender are recorded from the infant’s medical record by the study nurses at the time of infant enrollment. Maternal demographic data are also collected including age, race, ethnicity and parity.

### Procedures

Admissions to the NICU are monitored daily by the study nurses who contact parents in person about the study when their infant is 24 to 48 hours old; most mothers are still in hospital at this time. Informed consent discussions take place in the private rooms with one of the study nurses, all of whom are experienced NICU nurses skilled in talking to families about preterm infants. Research equipment is available during the consent discussion and a doll is used to show placement of sensors. Parents are encouraged to handle equipment and ask questions. After obtaining written informed consent, the study nurse gathers demographic data and sets up the data collection file. Each infant is assigned a code number. The files are kept locked in the research setting with daily transfer to the study research office for safe storage.

#### Randomization to groups

A random assignment scheme was developed by the study statistician using a random number generator. Infants are assigned to groups at enrollment in equal numbers using 120 cards marked with one or other group contained in sealed envelopes and kept in a locked cabinet in the study office. Assignment to group is not blinded to parents, NICU staff, or the study nurses. The examiner for the major study outcomes is blinded to group assignment.

#### Data collection procedures

The principal investigator and the study nurses provide in-service instruction for unit staff at both study settings. Data collection is completed by the study nurses; however, NICU staff are instructed in how to provide the intervention for infants in the intervention group and to maintain appropriate clinical records. Parents and other family members of infants in the intervention group also receive instruction in providing the intervention.

### Observation feedings

The study nurses schedule observation feedings twice a week during Phase 2 using procedures developed in our previous studies [22]. Observation feedings are scheduled to be compatible with parent and nursing staff schedules. These feedings generally are scheduled at times parents are not present since ideally parents prefer to feed their infant and we do not wish to interfere with this important process. Parents may be present during an observation feeding but they do not participate in these feedings; since observation feedings occur only twice a week and only during Phase 2, this is not difficult to achieve. During observation feedings, the computer data acquisition system continuously records heart rate and sucking activity. The study nurse oversees data acquisition to ensure that clear signals are obtained; the electronic file can also be “marked” using pre-assigned event keys for changes in position and movements, stops for burps, and rest periods made at the discretion of the feeder. Study nurses also record the volume consumed for computation of feeding performance measurements of efficiency and percent consumed. Observation feedings involve two people–a nurse feeding the baby (feeder) and a study nurse.

Routine vital signs and basic care (e.g., diaper change) are completed by the study nurse who then applies the research equipment. The infant remains on the unit’s monitoring equipment for oxygen saturation, respiration and heart rate. The infant is loosely swaddled in a blanket in a flexed position and removed from the incubator. Once the nurse is seated with the infant the data acquisition system is started, providing a continuous recording of HR and sucking activity.

Experienced neonatal nurses who are trained in the feeding procedures feed the infants. The feeder will feed the infant using the prescribed formula or breast milk in a volufeeder. Lighting and sound levels in the room are recorded as these may affect infants’ feeding performance. The feeding continues until the infant completes the prescribed amount, has no sucking activity for 2 minutes, or shows signs of distress (e.g., bradycardia), whichever occurs first. The infant is offered burps and rest periods at the discretion of the nurse. When the infant has completed the feeding or the feeding is halted, the time is recorded and the data acquisition system stopped. The infant is returned to the incubator and research equipment removed. The amount of fluid remaining in the bottle is recorded for computer computation of feeding skill efficiency and percent consumed. If the infant does not consume the prescribed volume during feeding, the study nurse gives the remaining amount by gavage using Phase 1 procedures appropriate for group assignment.

### Data management and analysis

A relational database has been created. Monthly assessment of data entry processes and a quarterly audit of random samples for completeness are conducted. During the electronic data acquisition process, all sampled data from each of the physiologic channels are stored in a single file. To prepare these data for analysis, the data are digitally filtered to remove frequencies not part of the physiologic signal spectrum. The filtered signal is then applied to our algorithms resulting in the relevant parameters.

Descriptive statistics will be computed for all demographic data to describe the sample and check for missing and outlying data. Descriptive statistics will also be computed for all component measures of study variables. Transformations of non-normally distributed variables will be used for analyses as indicated. Because measures are repeated on the same infant, all analyses will take into account the dependency between measures. Because some infants may be unable to complete the study due to unexpected illness, there will be an “all-infants” dataset (all eligible) and a “per-protocol” dataset (all completers). An intent-to-treat analysis will be performed on the all-infants dataset using all measures obtained. An analysis on the “per-protocol” dataset will be performed using the data from the infants who completed the entire study. All results will be reported as described by the CONSORT guidelines [17]. Analyses will be performed using SAS (SAS Institute Inc., Cary, NC, USA) at an overall alpha = 0.05 significance level.

The primary aim states that infants who receive the PFE will have improved neurobehavioral organization at transition to oral feedings, NICU discharge, and 2 months corrected age (48 weeks PMA). The difference between the PFE and usual care groups on the NAPI will be tested using a repeated-measures ANCOVA. A mixed-model will account for the correlation between the measurements at each time point and allow for differential patterns of missing values at the three time points. A significant difference across these time points will be followed by separate comparisons at each time point; each will be performed at the *P* = 0.05 level of significance.

The secondary aims require similar comparisons between study groups on secondary outcomes (cognitive functioning, neurobehavioral development, and clinical outcomes). To test secondary aim 1, differences between the 2 groups on the cognitive outcome measure (BSIDIII cognitive subtest scaled score) at 6 months corrected age will be tested using an ANCOVA with morbidity (NMI) and birth gestation used as covariates. To test secondary aim 2, 4 analyses will be performed, one for each of the feeding-related neurobehavioral outcomes (sucking organization, 2 measures of feeding performance, and HRV). The modeling will be done as above with a repeated-measures mixed-model approach with covariates (birth gestation, morbidity). To test secondary aim 3, separate ANCOVA analyses of the clinical outcomes (time to full oral feeding and length of stay) will be used to compare the 2 groups with the birth gestation age and morbidity covariates.

The intent of the exploratory aim is to identify risk factors of poor neurobehavioral development and cognitive dysfunction in preterm infants. We will test the assumed comparability of randomly assigned groups prior to undertaking further analyses. Secondary analyses will focus on the interactions between risk factors and the intervention differences by first screening the risk factors for effects at *P* = 0.2 and then developing a single exploratory model that includes all of the risk factors that significantly influence the outcome differences between the groups. Additional analyses will focus on the findings for neurobehavioral development including sucking organization and feeding performance, HRV, and clinical outcomes, first by examining the relationships between the risk factors and the components of neurobehavioral development and then by assessing the relationships among the components of neurobehavioral development and the primary outcome measure, the NAPI score (neurobehavioral outcome). The final goal is to identify a model of risk factors, modifiers (measures of neurobehavioral development), and mediators (intervention) that have an effect on the differences between groups.

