Our intervention, a patterned feeding experience (PFE), is not currently used in most neonatal settings. The intervention is based on principles of neural plasticity and neuroprotection and is designed to take advantage of neuronal synaptic development and both experience-expectant and experience-dependent characteristics of the developing brain [13]. In addition, the intervention takes advantage of a regularly occurring caregiving and life-sustaining event in the life of an infant–feeding. The PFE intervention involves a continuity of tactile experiences associated with feeding to train and build neuronal networks supportive of the normal experience. There are virtually no accepted and no tested caregiver behaviors related to enteral feedings in preterm infants, although some recent research has produced evidence for a positive effect of greater caregiver sensitivity to the infant during feeding [14]. Theoretically, our intervention provided at a critical time in neurologic system development and associated with a recurring event such as feeding should enhance neural connections that may be important for later development, particularly language and other cognitive and neurobehavioral organization skills [15].

The overall objective of this study is to test the effect of a PFE from birth to NICU discharge for infants born at 32 weeks gestation and younger. The primary aim of the study is to test the effect of a PFE on neurobehavioral organization at 3 time points: the transition to oral feedings, NICU discharge, and 2 months corrected age (48 weeks PMA). Secondary aims are to test the effect of a PFE on 1) cognitive function at 6 months corrected age; 2) neurobehavioral development; and 3) clinical outcomes including time to first oral feeding, time to full oral feeding, and time to discharge. An exploratory aim is to describe the potential effects of perinatal and infant risk factors including immunologic and genetics influences on the outcome variables (neurobehavioral organization, cognitive function, neurobehavioral development, and clinical outcomes). We hypothesize that infants who receive the PFE will have improved neurobehavioral organization, cognitive function, neurobehavioral development, and clinical outcomes compared to infants who receive usual feeding care in the NICU.

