#### Power analysis

The proposed sample size for the study is based on associations between measures of feeding experience and components of neurobehavioral development and neurobehavioral organization discovered in our previous studies [18–21]. We anticipate 20 % attrition, primarily for medical conditions that arise or are diagnosed after enrollment. The sample size was determined by assuming each aim will be tested using 2-sided tests at *P* = 0.05. For the primary aim, we expect to detect an effect size of at least 0.7 standard deviation (SD) between groups on the final neurobehavioral score, with at least 90 % power using a 2-group *t*-test. However, a random effects model that takes into account the repeated measurements over time is proposed for the analyses of neurobehavior. Differences of the same effect size should improve the power to at least 95 % because of the additional number of observations. Although we have powered the study to test the primary aim, we also considered power for the additional aims. For secondary aim 1 involving a test of the effect of the intervention on cognitive function at 6 months, the same sample size analysis indicates a 2-unit difference (SD = 3) on cognitive development will be detected with 89 % power with only a 2-group *t*-test; the analysis of covariance (ANCOVA) should have more power. For secondary aim 2, the analyses and the sample size calculations are the same as with the primary aim. Secondary aim 3 will be tested in a manner similar to secondary aim 1 and so the sample size calculations should be similar. For the exploratory aim a sample of 96 infants in a test for zero correlation will provide at least 90 % power to detect *r* ≥ 0.26 and at least 80 % power to detect *r* ≥ 0.21.

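### The plan states an overall alpha of 0.05, but it tests each aim at the full two-sided 0.05 and runs at least seven secondary comparisons with no order or adjustment, so that overall level is not held

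*Protocol article*

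**What the plan says.** All references are to the protocol article.

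- **Data management and analysis** sets the significance level for the analyses: "at an overall alpha = 0.05 significance level".
- **Power analysis** sets the level aim by aim: "The sample size was determined by assuming each aim will be tested using 2-sided tests at *P* = 0.05". It adds that the study is powered for the primary aim and that power for the other aims was also considered. For secondary aim 1 it gives 89 % power for a 2-unit difference with SD 3.
- **Data management and analysis** then lists the secondary tests. Aim 1 is one ANCOVA on the Bayley cognitive scaled score. For aim 2: "To test secondary aim 2, 4 analyses will be performed, one for each of the feeding-related neurobehavioral outcomes". Aim 3 is handled thus: "separate ANCOVA analyses of the clinical outcomes (time to full oral feeding and length of stay) will be used to compare the 2 groups".
- **Background** frames all of these as directional expectations: "We hypothesize that infants who receive the PFE will have improved neurobehavioral organization, cognitive function, neurobehavioral development, and clinical outcomes".

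The exploratory label is kept for the separate risk-factor aim. The only gate stated is inside the primary aim, where a significant result across time points precedes the comparisons at each time point. No sentence links the secondary tests to the primary result or to one another.

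**The concern.** In a plan with several aims, an overall alpha will usually be read as the error rate across the set of tests. If each aim has its own undivided 0.05, and two of the three secondary aims contain several parallel tests, the error rate across the set exceeds 0.05 unless an order or adjustment is imposed. The article states neither.

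This affects what may be claimed at the end. Suppose the NAPI result is negative and one secondary outcome, say the Bayley score, gives P = 0.03. The Power analysis wording lets that count as a positive test of its aim. The overall-alpha wording lets a reader believe it sits inside a controlled 5 % error rate, which it does not. The Discussion says the results could change neonatal feeding practice, so the distinction between a supportive and a confirmed finding has consequences.

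**Working it through.** **Inputs**

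- Evaluable sample: 120 enrolled with 20 % attrition (Sample; Power analysis), so 120 × 0.8 = 96, or 48 per group.
- Level per aim: two-sided 0.05 (Power analysis).
- Secondary tests (Data management and analysis): 1 + 4 + 2 = 7.
- Correlation between outcomes: not given. It is assumed common to all pairs and varied from 0 to 0.8.

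**Step 1. Reproduce the plan's own figures.** Two-group t-test with 48 per group, noncentral t:

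- Bayley: d = 2/3 = 0.667; noncentrality 0.667 × √(48/2) = 3.27. Power at two-sided 0.05 is 89.8 %, against 89 % stated.
- Primary: d = 0.7 gives 92.4 %, against at least 90 % stated.

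Both figures reproduce at an undivided two-sided 0.05. If alpha were split, Bayley power would be 76.2 % at 0.05/4 = 0.0125 (four aims) and 69.6 % at 0.05/7 = 0.0071 (seven tests). The power figures therefore do not rest on a split alpha.

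**Step 2. Error rate across the seven secondary tests when PFE has no effect.** With independent tests:

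- any false significant difference: 1 − 0.95^7 = 30.2 %
- a false result favouring PFE: 1 − 0.975^7 = 16.2 %

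With correlated tests, take seven normal test statistics with common correlation ρ and find the probability that at least one passes 1.96, in either direction or in the favourable direction only:

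| Assumed ρ | Any false significant difference | False result favouring PFE |
|---|---|---|
| 0 | 30.2 % | 16.2 % |
| 0.2 | 28.7 % | 14.7 % |
| 0.5 | 23.0 % | 11.5 % |
| 0.8 | 14.9 % | 7.4 % |

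The reference values for one two-sided 0.05 test are 5 % and 2.5 %. Both columns therefore run from about 3 to about 6 times the single-test rate (14.9/5 = 3.0 and 30.2/5 = 6.0; 7.4/2.5 = 3.0 and 16.2/2.5 = 6.5).

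**Step 3. Is seven the right count?** It is a minimum. The Background also names time to first oral feeding under secondary aim 3, and the analysis section does not list it. Counting it gives eight tests: 1 − 0.95^8 = 33.7 % for any difference and 1 − 0.975^8 = 18.3 % favouring PFE, if independent. Sucking organization and HRV are each described with three component measures, which could add more.

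**The case against.** **The two statements can be reconciled.** A fixed sequence tests each step at a full 0.05 and still holds an overall 0.05. It would be too strong to say that the statements cannot both be true, or that the 89 % power figure proves multiplicity is uncontrolled, because a fixed sequence would be planned with the same power figure. This stands. But the article states no sequence, and a sequence of aims would still need a rule for the four parallel tests in aim 2 and the two in aim 3.

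**Multiplicity rules for secondary outcomes are commonly left to the SAP.** An article that was merely silent would give no ground for a finding. This one is not silent: it asserts an overall level that the tests it describes do not deliver.

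**The word overall may only mean the general significance level.** It stands in the sentence naming the software, and the time-point comparisons that follow are each set at 0.05. This reading is plausible and limits the seriousness of the point. It also shows that the wording needs correcting, since a reader may equally take it as control across the family.

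**The outcomes are already ranked.** They are called secondary, and the study is powered for the primary aim. That is a fair reason not to demand formal gatekeeping. It does not say what may be claimed from a secondary result after a negative primary one.

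**Stronger readings a reader might infer.** One is that there is about a one-in-four chance of a false secondary benefit. The 23 % behind it counts differences in either direction and needs an assumed correlation of 0.5; in the favourable direction the figure there is 11.5 %. Another is that a Bayley P of 0.03 could never be positive under real error control. It could be, if Bayley were tested after a significant primary result in a fixed sequence, or under Holm if enough of the other P values were very small.

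**Conclusion.** The point holds in a limited form. The stated overall alpha of 0.05 does not match a plan with a full two-sided 0.05 per aim and at least seven secondary tests without order or adjustment. If PFE has no effect, the chance of at least one false significant secondary difference is about 15 % to 30 %, and of one favouring PFE about 7 % to 16 %, over assumed common correlations from 0.8 down to 0. These ranges rest on the plan's own count of seven, a common correlation that the document does not supply, and no true effect on any secondary outcome.

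The primary test and the stated power figures for the primary and Bayley comparisons are not put in doubt by this point. The documents do not show that the trial intends to claim benefit from a secondary result alone; the wording leaves that open.

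**What to change.** In Data management and analysis, replace the overall-alpha phrase with wording such as:

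*Two-sided 0.05 applies to the primary NAPI test. Secondary outcomes are each tested at two-sided 0.05 without control for multiplicity, are reported with 95 % confidence intervals, and are interpreted as supportive. No confirmatory claim of benefit will rest on them alone.*

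If the sponsor wants confirmatory secondary claims under an overall 0.05, one option is a prespecified sequence: the primary test, then Bayley at 0.05, then Holm over the remaining tests. Bayley keeps its stated 89 % power (89.8 % recomputed) only once the primary test is passed. The sequence would also need a single defined primary NAPI test and a fixed list of the remaining tests, including whether time to first oral feeding is one of them. Statisticians could reasonably choose another scheme.

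Cost of the main change: a few sentences, with no new data and no more infants. The downside is that a lone secondary P below 0.05 can no longer be presented as confirmed benefit. Under the optional sequence, Bayley cannot be confirmed if the primary test fails, and the tests placed under Holm lose some power.

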**Methods:**

This trial uses an experimental, longitudinal, 2-group design with 120 preterm infants. Infants are enrolled within the first week of life and randomized to an experimental group receiving a patterned feeding experience from the first gavage feeding through discharge or to a control group receiving usual feeding care experience. The intervention involves a continuity of tactile experiences associated with feeding to train and build neuronal networks supportive of normal infant feeding experience. Primary outcomes are neurobehavioral organization as measured by Neurobehavioral Assessment of the Preterm Infant at 3 time points: the transition to oral feedings, NICU discharge, and 2 months corrected age. Secondary aims are cognitive function measured using the Bayley Scales of Infant and Toddler Development, Third Edition at 6 months corrected age, neurobehavioral development (sucking organization, feeding performance, and heart rate variability), and clinical outcomes (length of NICU stay and time to full oral feeding). The potential effects of demographic and biobehavioral factors (perinatal events and conditions of maternal or fetal/newborn origin and immunologic and genetic biomarkers) on the outcome variables will also be considered.

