#### Prenatal risk factors

Maternal risk factors associated with neurodevelopmental outcomes include premature rupture of the membranes, pregnancy-induced hypertension, antenatal steroid or selective serotonin re-uptake inhibitor treatment, parity, chorioamnionitis, or diabetes mellitus [24, 25]. These data are included in the infant’s record and will be recorded after enrollment. Fetal or infant risk factors are intrauterine growth restriction, low 5-minute Apgar score, metabolic or respiratory acidosis within the first 24 hours of life, sepsis as defined by positive cultures, and evidence of intraventricular hemorrhage or periventricular leukomalacia on early and late cranial ultrasounds, which are routinely obtained in our setting at 2 weeks of life and at 34 to 36 weeks PMA [26, 27]. Data on these risk factors are available in the infant’s medical record and will be recorded by the study nurses. We will collect data for computing severity of illness using the Neonatal Medical Index (NMI), a tool we have used in previous studies [28]. The NMI summarizes infants’ medical condition with classifications ranging from 1 for infants born weighing ≥ 1000 g and without major complications to 5 for infants born weighing < 1000 g and with very serious complications. The scale distinguishes between the neurobehavioral performance of infants with varying degrees of illness and predicts developmental progress at 12, 24, and 36 months of age.

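### The secondary-aim analyses adjust for a complication-based morbidity score that is not limited to information before randomisation, so part of any PFE effect may be adjusted away

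*Protocol article*

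**What the plan says.** All three secondary aims adjust for morbidity (Protocol article, Data management and analysis):

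- **Aim 1**, Bayley cognitive scaled score at 6 months corrected age: "tested using an ANCOVA with morbidity (NMI) and birth gestation used as covariates".
- **Aim 2**, sucking, feeding performance and heart rate variability: a "repeated-measures mixed-model approach with covariates (birth gestation, morbidity").
- **Aim 3**, time to full oral feeding and length of stay: ANCOVAs that "compare the 2 groups with the birth gestation age and morbidity covariates".

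Only aim 1 names the NMI. Since that sentence equates morbidity with the NMI, aims 2 and 3 very probably mean the same score.

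The score itself is described under Prenatal risk factors: "We will collect data for computing severity of illness using the Neonatal Medical Index (NMI"). Its classes run from 1 (1000 g or more at birth, no major complications) to 5 (under 1000 g "and with very serious complications"). No scoring date or cut-off is given.

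On timing, the Abstract (Methods) says "Infants are enrolled within the first week of life and randomized". The Intervention section starts Phase 1 within 24 hours of the first gavage feeding, generally before 72 hours of life, and allows it to last up to 12 weeks. PFE then continues to discharge.

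**The concern.** A covariate in a randomised comparison should be fixed before treatment can influence it. An infant can be classed as free of major complications only once the period in which they occur has passed, and for this population most of that period follows randomisation. The Power analysis section itself expects 20% attrition, mainly from medical conditions that appear or are diagnosed after enrolment.

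The trial's rationale leaves room for treatment to act on that morbidity. The Abstract's background says neuroprotective strategies can halt the progression of brain lesions, and the Background and Discussion present PFE as such a strategy. A full-stay NMI could then lie on the path from PFE to the outcome. Conditioning on it would have two consequences:

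- the estimate would no longer be the total effect of PFE, because the part that runs through morbidity is taken out;
- unmeasured causes shared by morbidity and outcome could bias what is left.

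This would apply to the Bayley, feeding and heart rate variability, and clinical-outcome comparisons alike. Birth gestation is a true baseline covariate and is not in question.

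**Working it through.** **Inputs from the Protocol article**

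- 120 infants, 60 per group (Sample); 20% attrition (Power analysis). 120 × 0.8 / 2 = 48 per group.
- Aim 1: difference 2 units, SD 3, two-sided 0.05, stated power 89% with a t-test (Power analysis). Standardised effect 2/3 = 0.667 SD.

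**Inputs assumed, not in the documents**

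- *a*: reduction in NMI caused by PFE, in within-arm SD; range 0 to 0.5.
- *b*: within-arm loss of Bayley score per SD of NMI, in SD; 0.5.

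**Step 1: the plan's own figure.** Noncentrality = 0.667 × √(48/2) = 3.27 on 94 degrees of freedom, giving power 89.8% (normal approximation 90.4%). The stated 89% reproduces to within two points.

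**Step 2: the adjusted effect.** Adjusted effect = total effect − *a* × *b*.

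**Step 3: its standard error.** The residual SD after adjustment is √(1 − 0.5²) = 0.866. Correlation between arm and NMI inflates the variance by 1 + *a*²/4. So SE = 0.866 × √(2/48) × √(1 + *a*²/4), and power comes from the noncentral t on 93 degrees of freedom. Birth gestation is left out for simplicity.

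| NMI shift *a* (SD) | Effect removed (SD) | Adjusted effect (SD) | In scaled points (× 3) | SE | Power |
|---|---|---|---|---|---|
| 0 | 0 | 0.667 | 2.00 | 0.177 | 96% |
| 0.1 | 0.05 | 0.617 | 1.85 | 0.177 | 93% |
| 0.2 | 0.10 | 0.567 | 1.70 | 0.178 | 88% |
| 0.3 | 0.15 | 0.517 | 1.55 | 0.179 | 82% |
| 0.5 | 0.25 | 0.417 | 1.25 | 0.182 | 62% |

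The first row is also the result for an equally predictive covariate that treatment cannot affect: the full 2 units at about 96%. Adjusted power falls below the unadjusted 90% once the shift reaches roughly 0.18 SD.

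**Step 4: check by simulation in NMI classes.** With an assumed NMI SD of 1.2 classes, a shift of half a class and a slope of 1 scaled point per class, the formula gives 2 − 0.5 × 1 = 1.5 points. In 4,000 simulated trials of 48 per group the mean adjusted estimate was 1.51, against 2.01 unadjusted.

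**The case against.** The strongest reply is that the article never says when the NMI is scored. If it were computed only from data before randomisation, the problem would vanish, and the scoring window of a covariate may be left to a fuller document. That limits the point: it is not established that the analysis will use post-randomisation morbidity. It does not remove it. The article does fix the covariate, describes it by complications, and gives no limit that would make it a baseline measure.

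Four stronger readings are tempting but unsupported:

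- *The late ultrasounds show that the NMI is scored late.* The section lists "early and late cranial ultrasounds, which are routinely obtained in our setting at 2 weeks of life and at 34 to 36 weeks PMA" among separate infant risk factors and introduces the NMI afterwards. It does not say that these scans feed the score.
- *PFE is expected to lower the NMI.* Neonatal complications are not among the hypothesised outcomes; the lesion statement is general background; and part of the NMI is birth weight, which PFE cannot change. The path is plausible, but its existence and size are assumptions.
- *Adjustment necessarily costs power.* Under the assumed slope it gains power while the shift is below roughly 0.18 SD. This is the benefit the Power analysis section expects from ANCOVA. Gained power does not, however, restore the part of the effect that was removed.
- *The primary aim or the 89% figure is wrong.* The NMI is not named for the primary analysis, and the 89% reproduces.

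It is also fair to say that the NMI was chosen as a tool the group has used before and that is stated to predict development at 12 to 36 months. That supports its prognostic value, not its use as an adjustment covariate if it is measured after treatment starts.

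**Conclusion.** The point holds in conditional form. The secondary-aim models (ANCOVA for aims 1 and 3, a mixed model for aim 2) adjust for a morbidity score that, on its natural reading, includes events during the intervention. If PFE alters that morbidity, the adjusted comparison understates a benefit by shift times slope and may be biased further; if it does not, this attenuation is zero.

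The size rests on assumptions. For aim 1, at a slope of 0.5 SD, shifts of 0.1 to 0.5 SD remove 7.5% to 37.5% of the planned effect (0.05/0.667 to 0.25/0.667). The same mechanism applies to aims 2 and 3, provided their morbidity covariate is the NMI; no figures were derived for them. This is worth correcting because a safer covariate set is already available from recorded data, not because bias has been shown.

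**What to change.** In Data management and analysis, state for all three secondary aims that the adjustment covariates in the group comparisons use only information available at randomisation. These would be birth gestation plus one of:

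- the NMI scored solely from data recorded before randomisation; or
- baseline severity measures already collected, such as birth weight and 5-minute Apgar score.

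Name the covariate explicitly for aims 2 and 3, and add the scoring time to the NMI description under Prenatal risk factors. Keep any NMI covering the full stay for description and for the exploratory aim.

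The cost is wording, plus scoring at one fixed time from the record if the NMI is retained. Sample size, visits and measures do not change. The downside is that an early severity measure may explain somewhat less outcome variance than a full-stay score, so the gain in power from adjustment may be smaller than the 96% row suggests. The article does not report how well an NMI cut off at randomisation predicts development, which is a reason to consider the simpler baseline measures.
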